4.3.3　　At revision of the informed consent form

If the informed consent form is revised, the investigator, etc. should obtain the subject’s consent again.

1. Study drugs

Voltaren^®^ Tablets 25 mg (containing 25 mg of diclofenac sodium in 1 tablet)

Amitiza^®^ Capsules 24 µg (containing 24 µg of lubiprostone in 1 capsule)

1. Study design
   1. Study design

Open-label, randomized, parallel-group comparison study

For the first 6 subjects (3 subjects in each group) after the start of the study, the study treatment period or non-treatment period will be 28 days in this study. For the 7th subject and after that, the study treatment period or non-treatment period will be determined to be either 14 days or 28 days based on the results of the 6 subjects. If there is no difference in the 14-day treatment between the two groups but it is judged that there may be a tendency of difference in the 28-day treatment between the two groups, the study treatment period will be determined to be 28 days for the 7th subject and after that. In other cases, the study treatment period will be determined to be 14 days for the 7th subject and after that.

- 1. Dosage and administration of the study drug

Subjects will orally receive one capsule of Amitiza once daily after lunch for 14 days or 28 days.

- 1. Study registration

**This study will be registered to the UMIN Clinical Trials Registry and the information on the study will be made public. The clinical study registration will be done before registration of the first subject.**

- 1. Target sample size

35 subjects

- 1. Flow chart

*1: Lactulose/mannitol test, measurement of endotoxin activity in blood, intestinal flora test

*2: For the 7th subject and after that, the study treatment period (non-treatment period) will be determined to be either 14 days or 28 days based on the results of the first 6 subjects (3 subjects in each group).

Visit (1)

Visit (2)

Visit (3)

Study drug treatment group

Control group

Explain and obtain the consent

Medical examination, physical findings, etc.

Case registration

Administer diclofenac

Allocation

Tests for intestinal permeability^*1^

Tests for intestinal permeability^*1^

Administer the study drug

Not administer

←14 or 28 days*^2^→

7 days

←14 or 28 days*^2^→

Tests for intestinal permeability^*1^

Up to the first 6 subjects

Visit (1)

Visit (2)

Visit (3)

Visit (4)

Study drug treatment group

Control group

Explain and obtain the consent

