- - - 1. Subjects take diclofenac sodium and study drug according to the instructions given by the investigator, etc.
      2. If a subject missed (could not) to take study drug after lunch, he/she takes it after supper. If he/she missed (could not) to take study drug after supper, he/she takes no study drug on that day.
      3. During the study period, combined treatments [medications (including supplements) and therapies] are prohibited, unless the investigator, etc. considers that use of combined treatment is necessary for treating adverse event(s) that occurred in a subject(s) during the course of the study.
      4. If a subject experienced any abnormality during the study period, he/she must inform the investigator, etc. of it.
      5. Any subject must not drink a large of alcohol during the study period.
      6. It is not allowed to take any food or drink from 21:00 onward on the day before and the day when lactulose/mannitol test is performed. However, a small amount of drink without sugar content is allowed.

1. Items and time points for investigations/examinations
   1. Patient characteristics

Investigation items: date of birth, gender, height, weight, complication, past medical history, history of allergy, concomitant drug, frequency of bowel movement, stool condition, with or without use of purgative

Target groups: study drug group, control group

Time points of investigation: Screening period

- 1. Vital signs

Investigation items: blood pressure, pulse rate

Target groups: study drug group, control group

Time points of investigation: screening period, at the time when an adverse event occurred, at the time of discontinuation

- 1. Physical findings

Investigation items: subjective or objective findings, adverse events, nausea, frequency of bowel movement, stool conditions

Target groups: study drug group, control group
Time points of investigation: screening period, period for treatment with diclofenac, period for treatment with study drug, at the time of discontinuation

- 1. Compliance to diclofenac

Investigation items: treatment period, daily dose, cessation/discontinuation of medication, reason of cessation/discontinuation of medication, reason for change

Target groups: study drug group, control group

Time points of investigation: Period for treatment with diclofenac

- 1. Compliance to study drug

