Investigation items: treatment period, daily dose, cessation/discontinuation of medication, reason of cessation/discontinuation of medication, reason for change

Target groups: Study drug treatment group

Time points of investigation: Period for treatment with study drug

- 1. Lactulose/mannitol test

Target groups: study drug group, control group

Time points of investigation: screening period, period for treatment with diclofenac, period for treatment with study drug, at the time of discontinuation

- 1. Endotoxin activity in blood

Target groups: study drug group, control group

Time points of investigation: screening period, period for treatment with diclofenac, period for treatment with study drug, at the time of discontinuation

Volume of blood to be collected: 2 mL in each time

- 1. Intestinal flora

Target groups: study drug group, control group

Time points of investigation: screening period, period for treatment with diclofenac, period for treatment with study drug, at the time of discontinuation

1. Endpoints
   1. Efficacy endpoints

Primary endpoint: Permeability of the small intestine using the lactulose/mannitol test

Secondary endpoints: endotoxin activity in blood, changes in intestinal flora

- 1. Safety endpoints

Adverse events, adverse reactions

1. Adverse events
   1. Adverse events

An adverse event is defined as any untoward medical occurrence (including abnormal laboratory findings) in a subject and which does not necessarily have to have a causal relationship with study drug. In this study, adverse events will be collected during the period from the start of treatment with diclofenac sodium to the end of treatment with study drug.

Adverse events will be assessed based on the clinical symptoms observed in subjects.

All adverse events will be documented by the investigator, etc. on the case report form to record the dates of its occurrence and resolution, its seriousness and severity, whether the subject was treated or not, its outcomes and the results of evaluation of causal relationship between the event and study drug.

- 1. Serious adverse events

A serious adverse event includes those described below.

- - - 1. Death
      2. Any adverse event which may lead to death
      3. Any adverse event which requires admission to a hospital or clinic, or prolongation of existing hospitalization (excluding hospitalization for routine tests)
      4. Disability
      5. Any adverse event which may result in disability

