An unexpected adverse reaction is that which is not listed in the Interview Form of study drug (2014) or that which is listed in the Interview Form but its nature or severity is different from that described in the Interview Form.

- 1. Expected adverse reactions of study drug

Expected adverse reactions of Voltaren include the following events [based on the Interview Form of study drug (2015)].

Among the 1,474 subjects investigated until the approval, 239 adverse reactions were observed in 160 subjects (10.85%). Gastrointestinal symptoms such as gastric distress occurred in 139 subjects (9.43%) as major symptoms. Other symptoms included edema observed in 14 subjects (0.95%) and skin symptoms such as rash in 23 subjects (1.56%).

In the post-marketing drug-use result survey, 4,545 adverse reactions were observed in 2,749 (7.71%) out of the 35,653 subjects. As symptoms, gastrointestinal symptoms were observed in 2,365 subjects (6.63%) followed by general symptoms such as edema in 215 subjects (0.60%) and skin symptoms in 172 subjects (0.48%).

Reports of gastric ulcer and liver disorder as other adverse reactions accounted for below 0.1%.

Expected adverse reactions of Amitiza include the following events [based on the Interview Form of study drug (2014)].

Adverse reactions including abnormal laboratory findings were found in 196 (62%) /315 subjects who received study drug at a dose of 48 μg/day (24 μg b.i.d.) in 3 Japanese clinical studies. Most commonly observed adverse reactions included diarrhea in 95 subjects (30%) and nausea in 73 subjects (23%).

1. Study termination criteria in subjects

The study will be discontinued for the subject who meets any of the following criteria.

- - - 1. The subject himself offered to withdraw from the study participation
      2. The subject who could not comply with the prescribed administration of diclofenac sodium and study drug
      3. The subject for whom the prescribed test was not performed
      4. The subject who was judged impossible to move to the study period by the investigator, etc.
      5. The subject who turned out that he did not meet the inclusion criteria or violated the exclusion criteria after the start of the study
      6. The subject who developed an adverse reaction that falls under the category of Grade 2 or higher adverse reaction according to CTCAC v4.0 (moderate or severe prescribed in Section 11.6)

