      7. The subject for whom the investigator, etc. judged that the study should be discontinued

If this study is discontinued, the test after discontinuation will not be conducted as a rule unless the subject requests such test.

1. Compensation for research-related health injuries

In the event of research-related health injury, the study site must take necessary and adequate measures including medical treatments for the injury. On this occasion, if the principal investigator considers that the health injury is associated with the proper use of study drug and that there is causal relationship between the injury and study drug, the investigator is responsible for compensation. However, medical care cost and medical allowance will not be covered. If the health injury is considered attributable to the subject’s intention or serious mistake, the compensation cost may not be covered.

The principal investigator take out insurance designating the investigator and study site as persons insured, in order to take measures for liability of compensation of health-related injury associate with study drug.

1. Ethical and scientific conduct of the study
   1. Compliance with the declaration of Helsinki

The study will be conducted according to the declaration of Helsinki, ethical guidelines of clinical studies and the clinical protocol.

- 1. Ethical committee
     - 1. Prior to conducting the study, the principal investigator will be judged by ethical committee of the study site, and performs the study after approved by the committee.
       2. When provided with new information relating to protocol amendment or safety, the principal investigator requests of the ethical committee to review whether the study can be continued or not.
       3. In order to undergo continued review by ethical committee, the principal investigator reports in writing the status of implementation of the study to the head of study site once a year or according to the procedures of the study site.

1. Approval of, compliance with and amendment of study protocol
   1. Approval of study protocol

Prior to the conduct of the study, the principal investigator will obtain an approval of the contents of study protocol from the head of the study site.

- 1. Compliance with clinical protocol

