- 1. Handling of personal data

For enrollment of a subject and preparation of his case report form, the investigator, etc. identify him by the subject identification code to retain the information as linkable anonymized data. Thus, personal data of a subject must be handled with caution.

1. Storage and destruction of records
   1. Storage of records

The investigator, etc. retains following records and documents for 5 years: case report forms, laboratory data, documents of ethical committee, documents on subject’s consent, documents on treatment with study drug and the study-related data.

- 1. Destruction of records

After completion of the storage period of records, the study-related data will be destroyed adequately, not to leak such secrets as personal data of subjects.

1. Statistical analysis

In this study, statistical analysis will be performed mainly for the following items. Details of the statistical design will be described in the statistical analysis plan.

- 1. Demographic characteristics

In addition to summary of subjects, summary statistics of demographic variables (including gender and age) of subjects will be shown.

- 1. Analysis set

Analysis set of the study will be Full analysis set (FAS) consisting of all subjects enrolled in the study, except for those described below.

• Subjects who were found to be ineligible for the study after the registration

• Subjects who took no study drug

• Subjects who had no efficacy data

- 1. Analysis methods for efficacy endpoints
     - 1. Primary endpoint

The summary statistics will be calculated for the permeability of the small intestine at baseline and after treatment respectively (mean, median).

For the primary analysis, (permeability of the small intestine after treatment - permeability of the small intestine at baseline) will be sought for each subject and the corresponding Wilcoxon test will be performed. The significance level will be 5% on both sides. For reference, the 2 groups will be compared using the Analysis of Covariance with permeability of the small intestine at baseline as a covariate.

- - - 1. Secondary endpoint

For endotoxin activities in blood and changes in the intestinal flora, too, (values after treatment - values at baseline) will be sought for each subject and the paired Wilcoxon test will be performed. The significance level will be 5% on both sides. For reference, the 2 groups will be compared using the Analysis of Covariance with baseline value as a covariate.

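### Removing treated subjects from the study for missed dosing, as a rule without later tests, can lose the day 14/28 primary value in the treated arm only

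*Protocol*

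**What the plan says.** Section 12 of the protocol opens its list of criteria with "The study will be discontinued for the subject who meets any of the following criteria". Item 2 of the list, also item 2 of the discontinuation criteria in the Summary, is "The subject who could not comply with the prescribed administration of diclofenac sodium and study drug". Neither place says how many missed doses amount to non-compliance. Section 12 closes with "If this study is discontinued, the test after discontinuation will not be conducted as a rule unless the subject requests such test".

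Four other places bear on this:

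- Section 9.5 (compliance to study drug) is restricted: "Target groups: Study drug treatment group".
- Section 9.6 (lactulose/mannitol test) reads "Time points of investigation: screening period, period for treatment with diclofenac, period for treatment with study drug, at the time of discontinuation".
- Section 8.4 item 2 moves a dose missed at lunch to supper and then says "If he/she missed (could not) to take study drug after supper, he/she takes no study drug on that day".
- Section 22.3 bases the primary analysis on a change score: "permeability of the small intestine after treatment - permeability of the small intestine at baseline) will be sought for each subject".

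**The concern.** The criterion ends participation where stopping the capsule would do. Outcome collection then depends on adherence, and after allocation only one arm has anything to adhere to. Subjects who stop taking lubiprostone may well differ in outcome from those who continue. Mild diarrhoea or nausea, for example, would not reach the Grade 2 threshold of item 6 but could lead a healthy volunteer to stop. Losing such subjects turns the treated arm into a selected group while the control arm stays whole. The loss arises when data are collected, so the statistical analysis plan can describe it but not repair it. Losses through item 6 (moderate or severe adverse reactions) are a separate route and are not considered here.

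**Working it through.** The protocol states no figure to reproduce: the sample size rests on feasibility, with no effect size, SD or dropout rate. The check is first a reading of the rules, then an illustration of size.

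**Can the rule act in the control arm after allocation?**

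1. Section 8.2 places allocation after the 7 diclofenac days, so the diclofenac part of item 2 acts before allocation.
2. After allocation the controls receive no drug for 14 or 28 days (Section 8.2).
3. Study-drug compliance is recorded in the treatment group only (Section 9.5).
4. So no control can meet the study-drug part of item 2.

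**Is the day 14/28 value still collected?** Nothing in the protocol keeps a discontinued subject in follow-up to that visit, and Section 12 stops later tests as a rule. Section 9.6 lists a test at discontinuation, but it is taken on the stopping date.

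**Share of the arm per removed subject** (equal allocation assumed; the protocol gives a total of 30 in the sample-size section and 35 in Section 6):

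- total 30: 1/15 = 6.7%
- total 35, arm of 18: 1/18 = 5.6%
- first six, three per group: 1/3 = 33%

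**Shift of the treated mean.** If k of n treated subjects are removed and their mean change differs by d SD from that of the others, the mean of those who remain differs from the mean of the full arm by (k/n) × d. The values of k and d are assumptions.

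| k removed | n = 15, d = 0.5 | n = 15, d = 1 | n = 18, d = 0.5 | n = 18, d = 1 |
|---|---|---|---|---|
| 0 | 0 | 0 | 0 | 0 |
| 1 | 0.033 | 0.067 | 0.028 | 0.056 |
| 2 | 0.067 | 0.133 | 0.056 | 0.111 |
| 3 | 0.100 | 0.200 | 0.083 | 0.167 |

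**A second illustration.** Let a fraction q of the treated arm be lost, with correlation ρ between the tendency to stay and the outcome, and no true effect. The expected spurious difference is ρ × φ(z_q)/(1 − q), where φ is the normal density and z_q the q-quantile. The type I error is from 10,000 simulated two-sided 5% rank-sum tests between groups, starting from 15 per arm.

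| q | ρ = 0: bias, type I | ρ = 0.3: bias, type I | ρ = 0.5: bias, type I |
|---|---|---|---|
| 10% | 0 SD, 4.6% | 0.058 SD, 5.3% | 0.097 SD, 5.3% |
| 20% | 0 SD, 4.8% | 0.105 SD, 5.7% | 0.175 SD, 6.6% |
| 30% | 0 SD, 4.4% | 0.149 SD, 5.9% | 0.248 SD, 8.5% |

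The loss of precision is smaller. By the normal approximation, the difference detectable with 80% power is (1.960 + 0.842) × √(1/15 + 1/n_t). This is 1.02 SD with n_t = 15 treated subjects, 1.04 with 14 and 1.14 with 10.

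**The case against.** The strongest reply has five parts.

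- **The exit test.** Section 9.6 and the closing paragraph of Section 12 can be read together: a test on the day of stopping, none afterwards. The primary analysis speaks of a value after treatment and names no day, so an exit value might serve. This weakens the point but does not remove it. An exit value comes at a different time from the controls' day 14/28 value, when permeability may still be recovering from diclofenac.
- **The primary test.** Section 22.3 can be read as a paired Wilcoxon test within group, with the between-group covariance analysis for reference only. On that reading one-sided loss does not unbalance the primary test. It still selects within the treated arm and so distorts the paired test there. It also affects the covariance analysis and the comparison with untreated subjects that Section 1 sets as the aim.
- **The trigger.** A subject who skips a day as Section 8.4 directs is arguably following the prescribed dosing. This is a fair reading, and there is no contradiction between the two sections, but the text does not say so.
- **The size.** With 15 per arm the standard error of a difference in means is √(2/15) = 0.37 SD. The extreme tabulated shift for that arm size, 0.20 SD, is about half of that, and the bias is zero if loss is unrelated to outcome. This stands. Among the first six, a subject who fails between day 14 and day 28 has also already given his day 14 value.
- **The purpose.** A pilot may reasonably ask what the drug does in those who take it. However, the full analysis set in Section 22.2 does not exclude subjects for incomplete dosing, so the protocol's own analysis population does not call for their removal.

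**Conclusion.** The concern holds. After allocation, item 2 can remove only lubiprostone subjects, and as a rule their scheduled day 14/28 tests are then not done. The rule is fixed in the protocol, so this is not a detail left to the analysis plan.

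The size is unknown and may be small. It is zero if skipped days count as compliant and nobody else fails to comply. The shift of 0.03 to 0.20 SD for 1 to 3 of 15 removed rests on assumed counts and an assumed 0.5 to 1 SD difference. The most sensitive point is the first stage, "For the first 6 subjects (3 subjects in each group) after the start of the study". Its results decide whether all later subjects are treated for 14 or 28 days, and one removal leaves two treated subjects. The change is worth making because it costs little and each value counts in a trial of 30 to 35 subjects.

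**What to change.** In Section 12 item 2 and Summary item 2:

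- State that, after allocation, failure to comply with dosing stops the study drug only. The subject stays in the study, has the scheduled day 14/28 lactulose/mannitol, endotoxin and flora tests unless he withdraws consent, and is analysed in his allocated group.
- State that a day skipped under Section 8.4 item 2 does not by itself trigger the criterion.
- Exempt these subjects from the closing paragraph of Section 12.

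The diclofenac part, which acts before allocation, can stay as it is.

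The cost is protocol wording, since the day 14/28 visit is already scheduled. With the tests kept, loss for this reason falls to zero in both arms, apart from subjects who withdraw consent. The drawback is some dilution of the contrast, at most k/n if non-compliers gain no benefit at all: 1/15 = 6.7%, 2/15 = 13.3% or 3/15 = 20% of the effect.

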- - - 1. Administer diclofenac sodium (75 mg/day) three times a day after every meal for 7 days.
      2. After administering diclofenac sodium for 7 days, the investigator, etc. will perform medical examination and allocate the subjects who can move to the study period to either a study drug treatment group or a control group.
      3. The lactulose/mannitol test, measurement of endotoxin activity in blood, and intestinal flora test will be performed.

For the first 6 subjects (3 subjects in each group) after the start of the study, the study treatment period or non-treatment period will be 28 days. For the 7th subject and after that, the study treatment period or non-treatment period will be determined to be either 14 days or 28 days based on the results of the 6 subjects.

[Up to the first 6 subjects]

[Study period]

(In the case of the study treatment group)

- - - 1. Administer 1 capsule of the study drug once a day after lunch for 14 days. The subjects are instructed to comply with the “Rules to be followed by subjects”.
      2. After administering the study drug for 14 days, the investigator, etc. will perform medical examination, as well as lactulose/mannitol test, measurement of endotoxin activity in blood, and intestinal flora test.
      3. Administer 1 capsule of the study drug once a day after lunch for 14 days.
      4. After administering the study drug for 14 days, the investigator, etc. will perform medical examination, as well as lactulose/mannitol test, measurement of endotoxin activity in blood, and intestinal flora test.

(In the case of the control group)

- - - 1. The study drug will not be administered (for 14 days). The subjects are instructed to comply with the “Rules to be followed by subjects”.
      2. After 14 days, the investigator, etc. will perform medical examination, as well as lactulose/mannitol test, measurement of endotoxin activity in blood, and intestinal flora test.
      3. The study drug will not be administered (for 14 days).
      4. After 14 days, the investigator, etc. will perform medical examination, as well as lactulose/mannitol test, measurement of endotoxin activity in blood, and intestinal flora test.

[After the 7th subject]

[Study period]

(In the case of the study treatment group)

- - - 1. Administer 1 capsule of the study drug once a day after lunch for 14 days or 28 days. The subjects are instructed to comply with the “Rules to be followed by subjects”.

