- 1. Analysis methods for safety endpoints

The type, severity, and incidence of adverse events and adverse reactions that occurred will be calculated and compared between the 2 groups.

- 1. Design of sample size

This study will be conducted for healthy volunteers as pilot positioning. Because the prior data do not exist, the scheduled number of registered subjects will be 30 subjects who are considered to be collectable within the specified study period.

1. Financing source and conflict of interest associated with the study

The study is sponsored by Abbott Japan Co., Ltd. and will be conducted by Yokohama City University as a contract research by Abbott Japan Co., Ltd.

Responsible person for study will declare any conflict of interest according to conflict of interest management rules of the study site.

The investigator will prepare the database to be used in this study by making it anonymous and Abbott Japan Co., Ltd. can neither access it nor perform statistical analysis using the database. Evaluation and interpretation of the results of the study will be performed by the investigator. The results of the study will not be disclosed unless the written consent is obtained according to the confidentiality rules.

1. Expenses on study participation

A research cooperation expenditure will be 50,000 yen per subject.

The investigator will purchase diclofenac sodium and study drug which will be used in the study.

1. Publication of the results

Whatever the study results may be, the principal investigator will publish the results in a scientific journal or in a scientific meeting.

Until 60 days prior to the publication of the study results, the investigator or the study site will submit the manuscript with the same contents to Abbott Japan Co., Ltd. to request their review and comments.

1. Study organization
   1. Responsible person for study (Investigator)

Department of Gastroenterology and Hepatology Yokohama City University Hospital
Professor   [name]

- 1. Sub-investigator

Department of Gastroenterology and Hepatology Yokohama City University Hospital
Postgraduate     [name]

Department of Gastroenterology and Hepatology Yokohama City University Hospital
Medical advisor   [name]

Department of Gastroenterology and Hepatology Yokohama City University Hospital
Postgraduate    [name]

Department of Biostatistics, Yokohama City University Graduate School of Medicine
Professor   [name]

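### The only analysis set the protocol names carries efficacy-type exclusions, and safety has no set of its own, so some exposed subjects fall out of the adverse-event incidence

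*Protocol*

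**What the plan says.** Protocol section 22.2 (Analysis set) defines a single set: "Analysis set of the study will be Full analysis set (FAS) consisting of all subjects enrolled in the study, except for those described below". Three exceptions follow:

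- "Subjects who were found to be ineligible for the study after the registration"
- "Subjects who took no study drug"
- "Subjects who had no efficacy data"

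Section 22.4 (Analysis methods for safety endpoints) states the whole safety analysis in one sentence: "The type, severity, and incidence of adverse events and adverse reactions that occurred will be calculated and compared between the 2 groups". It names no population, and no safety set appears elsewhere in the protocol.

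Three other places determine who is affected:

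- Section 11.1 (Adverse events) opens the collection window before allocation: "adverse events will be collected during the period from the start of treatment with diclofenac sodium to the end of treatment with study drug".
- Section 8.2 (Study procedures) allocates only after the seven diclofenac days, when the investigator is to "allocate the subjects who can move to the study period to either a study drug treatment group or a control group".
- Section 12 (Study termination criteria in subjects) stops subjects with a Grade 2 or higher reaction and subjects found ineligible after the start. It adds that "the test after discontinuation will not be conducted as a rule unless the subject requests such test".

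**The concern.** Section 22.2 speaks of the study as a whole and stands ahead of both the efficacy and the safety methods. Its exceptions are criteria for an efficacy set. Applied to adverse events, they can remove people who were exposed and had an event. For two of the three routes, the reason for removal may be the event itself: a subject who tolerates diclofenac badly may not be allocated, and a subject with a Grade 2 or higher reaction is stopped.

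Safety is a stated endpoint. Healthy volunteers are given an NSAID in order to raise intestinal permeability, and section 22.4 promises incidence by severity. With a target of 30 to 35 subjects, losing even one or two from a denominator visibly changes a reported rate.

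**Working it through.** The protocol gives no figure to reproduce on this point. The check applies the three exceptions to each path a subject can take, then gauges the scale.

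**Step 1: two terms with more than one reading.**

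- *Study drug.* Section 1 (Background) uses the term for lubiprostone alone, and section 12 names diclofenac and study drug side by side. Section 5 (Study drugs) lists both products.
- *Efficacy data.* The efficacy measure in section 22.3 is an after-treatment minus baseline difference, so the term could mean a post-treatment value. It could also mean any value; under section 8.2 an allocated subject is tested at screening and after diclofenac.

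**Step 2: each path.**

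| Path | What the text does | Depends on a reading? |
| --- | --- | --- |
| A. Dosed, later found ineligible | First exception removes him with his events | No |
| B. Took diclofenac, not allocated | Second exception removes him if study drug means lubiprostone. If diclofenac counts, he may stay in the set, but he is in neither of the two groups that section 22.4 compares | The route does; the result (not counted) does not |
| C. On lubiprostone, stopped for a Grade 2 or higher reaction, no later test | Third exception removes him if a post-treatment value is required; he stays if any value suffices | Yes |
| D. Event in the diclofenac week, then allocated to lubiprostone and tested | Stays, unless later found ineligible | No |

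**Step 3: the test at discontinuation.** Section 9.6 (Lactulose/mannitol test) lists discontinuation as a test time point, while section 12 says that as a rule no test follows discontinuation. How many subjects follow path C depends on which passage is applied.

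**Step 4: scale of path C, under the post-treatment reading only.** Take n = 17 on lubiprostone (35/2 = 17.5, rounded down). Let k be the number stopped for a Grade 2 or higher reaction and left untested; k is an assumption. If these are all the Grade 2 or higher reactors, the rate among all treated is k/n and the reported rate is 0/(n − k).

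- k = 1: 1/17 = 5.9%
- k = 3: 3/17 = 17.6%, reported as 0/14
- k = 5: 5/17 = 29.4%

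For reactions of any grade, the rate in section 11 (Expected adverse reactions) is 196/315 = 62.2%, and 0.622 × 17 = 10.6, taken as 11. With k = 3, 11/17 = 64.7% becomes 8/14 = 57.1%. With 30 registered and n = 15, 9 reactors and k = 3, 9/15 = 60.0% becomes 6/12 = 50.0%.

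The 62% was seen at 48 µg/day and includes abnormal laboratory findings. This trial gives one 24 µg capsule daily and assesses events on clinical symptoms. The rate serves only to set a scale.

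**Step 5: scale of path B.** The diclofenac reaction rates in section 11 are 7.71% and 10.85%. Expected reactors are N × p: 30 × 0.0771 = 2.3 up to 35 × 0.1085 = 3.8. The chance of at least one, 1 − (1 − p)^N, is 0.91 to 0.98. These figures count reactors, not subjects who fail to be allocated. The latter number is unknown and may be smaller.

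**Step 6: path A.** The protocol gives no rate of late-found ineligibility, so no size can be put on it.

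**The case against.** The best case for the protocol has five parts.

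- *The SAP may settle it.* Section 22 sends details to the SAP, which is not at hand, and a safety population is often defined there. Section 22.4 does not cite the FAS and speaks of events that occurred. This limits the point: it cannot be said that events will be dropped. It does not remove it, because the protocol does not leave the set open. It names one set for the study, with exceptions, and an SAP with a separate safety set would depart from that text.
- *Path B is partly a matter of grouping.* A subject who is never allocated cannot enter a two-group comparison under any analysis set. That stands, and it is why the fix needs a single-group table for the diclofenac week. The lubiprostone-only reading would also remove the untreated control group under the second exception. That is a separate defect, and path B is lost without relying on it.
- *Path C is conditional.* That stands in full. Allocated subjects already have test results, section 9.6 lists a test at discontinuation, a subject may ask for one, and the first six have a day-14 test, so a stop after that leaves a post-treatment value. A reader might infer that the moderate or severe rate on lubiprostone is forced to zero. The text supports that only if a post-treatment value is required and every such subject leaves untested.
- *Removal is not always linked to harm.* That stands for path A: late-found ineligibility is not selection on an adverse event.
- *This is a feasibility-sized pilot.* The primary endpoint is untouched, every event goes on the case report form, and event reporting under section 11.3 does not depend on the analysis set. That stands and lowers the priority.

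**Conclusion.** The point holds as a badly fixed statement that should be corrected. It is not a fatal flaw. As written, one set with efficacy-type exceptions serves the whole study. Dosed subjects later found ineligible are removed with their events. Subjects who took diclofenac and were not allocated are left out of the safety result, whichever meaning of study drug is used. Subjects stopped for a Grade 2 or higher reaction without a test are removed only if the efficacy-data exception requires a post-treatment value; in that case the reported moderate or severe rate would be too low.

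The size is not known. The range of 6% to 29% hidden rests on an assumed 1 to 5 subjects among 17 and on that one reading; it is not a forecast. A reader might also infer that safety data would be lost for good. They would not: the events are recorded, and only the planned tabulation leaves them out.

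**What to change.** - In section 22.2, state that the three exceptions apply to the efficacy analyses only, and say whether the efficacy-data exception means no post-treatment value or no value at all.
- In section 22.2, add a safety analysis set of every subject who took at least one dose of diclofenac, regardless of later-found ineligibility or missing efficacy data.
- In section 22.4, use that set: report the diclofenac week as one group in all dosed subjects, and compare events after allocation by group in all allocated subjects.
- Reconcile section 9.6 with section 12 on the test at discontinuation.

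The cost is about two sentences of protocol wording, one extra safety table and possibly slightly less favourable reaction rates. No new data are needed, since the events are already on the case report form.
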